## Abstract

**Introduction:**

Currently, we are unable to accurately predict mortality or neurological morbidity following resuscitation after paediatric out of hospital (OHCA) or in-hospital (IHCA) cardiac arrest. A clinical prediction model may improve communication with parents and families and risk stratification of patients for appropriate postcardiac arrest care. This study aims to the derive and validate a clinical prediction model to predict, within 1 hour of admission to the paediatric intensive care unit (PICU), neurodevelopmental outcome at 3 months after paediatric cardiac arrest.

**Methods and analysis:**

A prospective study of children (age: >24 hours and <16 years), admitted to 1 of the 24 participating PICUs in the UK and Ireland, following an OHCA or IHCA. Patients are included if requiring more than 1 min of cardiopulmonary resuscitation and mechanical ventilation at PICU admission Children who had cardiac arrests in PICU or neonatal intensive care unit will be excluded. Candidate variables will be identified from data submitted to the Paediatric Intensive Care Audit Network registry. Primary outcome is neurodevelopmental status, assessed at 3 months by telephone interview using the Vineland Adaptive Behavioural Score II questionnaire. A clinical prediction model will be derived using logistic regression with model performance and accuracy assessment. External validation will be performed using the Therapeutic Hypothermia After Paediatric Cardiac Arrest trial dataset. We aim to identify 370 patients, with successful consent and follow-up of 150 patients. Patient inclusion started 1 January 2018 and inclusion will continue over 18 months.

**Ethics and dissemination:**

Ethical review of this protocol was completed by 27 September 2017 at the Wales Research Ethics Committee 5, 17/WA/0306. The results of this study will be published in peer-reviewed journals and presented in conferences.

**Trial registration number:**

NCT03574025.

Strengths and limitations of this studyThis protocol has followed the international recommended Transparent Reporting of a multivariable prediction model for Individual Prognosis or Diagnosis guidelines for the derivation and validation of a clinical prediction model of neurodevelopmental outcome after paediatric cardiac arrest.A nationwide study which will efficiently combine routinely collected data through the existing, high-quality, Paediatric Intensive Care Audit Network database and a bespoke research database.Personalised recruitment and local follow-up will aim to maximise participant retention.The low incidence and wide variety of causes of paediatric cardiac arrest may restrict number of available patients and are potential limitations in prospective prognostic research in this population.Baseline neurodevelopmental status of patients will only be allocated retrospectively using the Paediatric Cerebral Performance Category tool.

## Introduction

### Paediatric cardiac arrest

Paediatric cardiac arrest (CA) is an uncommon but potentially catastrophic event for both children and their families. CA is defined as the cessation of cardiac mechanical activity occurring with absence of signs of circulation. Approximately 1500 infants or children per year suffer a CA in the UK and Ireland (RoI) with between 250 and 350 admitted to a paediatric intensive care unit (PICU) for postresuscitation care.^1^ Survival to PICU discharge for this population is achieved in 35%–45% patients admitted to PICU after an out of hospital CA (OHCA) and 45%–55% after in-hospital CA (IHCA). However, 50% of survivors are estimated to have ongoing neurodevelopmental disabilities despite advances in post-CA management.^2 3^ The high mortality and morbidity rates are often associated with the degree of brain injury from the hypoxic-ischaemic insult at the time of CA.

### Prognostication after CA

Clinicians are currently unable to accurately predict survival with a good neurodevelopmental outcome after CA with any certainty due to a lack of data.^4–6^ Clinicians can be pessimistic, optimistic or unnecessarily ambiguous in their predictions, and this affects the clarity of communication with families and the implementation of ongoing treatment plans.^4^ Improved prognostication is, therefore, a high priority for parents of children who have suffered a CA. In addition, early stratification of patients who may benefit from critical care interventions would also be a significant advancement in their treatment^7 8^ and has been lacking in major studies to date.^2 3^

Several prognostic factors are associated with survival following paediatric CA, such as patient age and pre-existing comorbidities,^9^ CA characteristics (location, initial CA rhythm, duration of CA, presence and actions of bystanders,^9 10^ physiological observations (eg, pupillary response, blood lactate, systolic blood pressure)^1 10 11^ and specific medical interventions.^11 12^ However, studies examining prognostic factors for good neurodevelopmental outcome are much less frequent.

The importance and weighting of these factors in prognosis decision making is complex and in 2010 the International Liaison Committee On Resuscitation (ILCOR) consensus statement identified a significant gap in knowledge in prognostic modelling with children^5^ with no additional ‘high-quality’ data to inform the 2015 guidance.^13^

### Rationale for study

Accurate early prediction of neurodevelopmental outcomes may reduce uncertainty and improve communication with families. It may also provide better risk stratification for clinical trials and individualised treatment of patients. Furthermore, we aim to gain a better understanding of the epidemiology and neurodevelopmental outcomes of children after CA in the UK and RoI.

## Methods and analysis

### Study aims

The aim of the NEUROlogical Prognosis After Cardiac Arrest in Kids study is to (1) derive a clinical prediction model using key factors prospectively collected from a cohort of patients, available within the first hour of PICU admission after paediatric CA to predict good neurodevelopmental outcome at 3 months, (2) externally validate the clinical prediction model using an existing paediatric CA dataset and (3) describe the current epidemiology of CA cases in the UK and Ireland (RoI).

### Study design

This study is a multicentre, nationwide, prospective observational study combining both registry and cohort data. See figure 1 for study overview.

**Figure 1 F1:**
[figure not shown]
NEUROPACK study overview: population, data collection tools and primary outcome. CPR, cardiopulmonary resuscitation; IHCA, in-hospital cardiac arrest; NEUROPACK, NEUROlogical Prognosis After Cardiac Arrest in Kids; OHCA, out of hospital cardiac arrest; PICU, paediatric intensive care unit; PlCANET, Paediatric Intensive Care Audit Network; NETPACK 3, PICANet Post Arrest Care in Kids audit; VABS II, Vineland Adaptive Behavioural Score 2nd ed.

### Setting

Patients will be enrolled from 24 PICUs within the UK and RoI. All study sites admit infants and children following CA and routinely submit audit data to the Paediatric Intensive Care Audit Network (PICANet) registry.

### Ongoing PICU registry: PICANet and NET-PACK 3

Since 2002, PICANet has prospectively collected demographic, diagnostic, and interventional data along with PICU survival outcomes for patients admitted to PICUs in England and Wales and now collects data for patients across the UK and RoI.^14^ This includes severity of illness variables to build the Paediatric Index of Mortality (PIM) risk-adjustment models.^15^

PICANet is also conducting an ongoing customised data collection of post-CA management: PICANet Post Arrest Care in Kids (NET-PACK 3) with data definition and data collection form (online supplemental materials 1 and 2). NET-PACK 3 customised data collection includes resuscitation variables available within a few hours of the CA. Data are either collected within 1 hour of admission onto PICU or within 1 hour of the attendance at the patient’s bedside of a specialist paediatric critical care team (eg, a specialised retrieval team travels to another hospital without a PICU). These variables include: (1) attempted bystander cardiopulmonary resuscitation (CPR), (2) duration of CPR, (3) requirement of CPR after arrival at emergency department, (4) number of doses of epinephrine (epinephrine) required and (5) initial presenting cardiac rhythm. These factors were chosen to comply with Utstein style CA reporting guidelines.^16 17^ PICANet collects survival to PICU discharge outcome data for all admissions.

10.1136/bmjopen-2020-037517.supp1Supplementary data

10.1136/bmjopen-2020-037517.supp2Supplementary data

## Eligibility for NEUROlogical Prognosis After Cardiac Arrest in Kids

### Inclusion

All patients aged 24 hours up to 16th birthday admitted to PICU after OHCA or IHCA will be included. CA will be defined as requiring >1 min CPR. Patients will be included if they require invasive (eg, via endotracheal or tracheostomy) mechanical ventilation at PICU admission.

### Exclusion

Exclusion criteria include CAs occurring within a PICU or neonatal intensive care unit. For children who survive to PICU discharge we will exclude patients where the local clinical team at participating sites feel inclusion is inappropriate and/or parent/guardian or family member of children are unable to understand the telephone questionnaires for neurodevelopmental outcome assessments in English. All patients under the age of 24 hours will be excluded due to potentially different aetiology of CA related to birth events.

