### Data collections

The ongoing NET-PACK 3 customised data collection and PICANet data collection for the PIM3 risk of mortality will be the data source for all the candidate variables in the NEUROPACK study. Linkage of individual patient NET-PACK 3 data with the collected neurodevelopmental outcome will be carried out for consented patients only. Pseudonymised data from NET-PACK 3 customised data collection and PICANET will be used for patients who die or for patients who survive and consent for follow-up assessment is not available.

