### Sample size

To reduce problematic bias and improve precision we aim for at least 10 events per variable considered for multivariable modelling.^23^ Following pilot data collection, we calculate 250 CA patients per year are admitted to 27 UK and RoI PICUs, 125 (50%) will survive to PICU discharge and 70 (30%) per year will survive with good neuro-developmental outcome. To test seven variables we estimate a requirement of 70 events (eg, patients with good neurodevelopmental outcome). One hundred per cent of non-survivors will be included (included in PICANet and NET-PACK 3 audit database). We anticipate 80% recruitment and consent rate of remaining survivors. We, therefore, require data collection over an 18-month period to recruit 370 patients. We anticipate that this would ensure successful consent and follow-up of 150 patients, of whom 75 patients are estimated to have a good neurodevelopmental outcome.

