### Final prognostic model

The optimised adjusted calibration slope will then be used as a uniform shrinkage factor. Each of the coefficients from the original model will be adjusted for by multiplying by the shrinkage factor. The intercept will also be adjusted to ensure calibration-in-the-large, the average predicted probability, is the same as the average observed probability.

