### Secondary analysis

Using the secondary outcomes, we will repeat the steps above to create a supplemental final prognostic model, for survival to PICU and survival to 3 months. In addition, we will create a prognostic model for good neurodevelopmental outcome using POPC and PCPC outcome scores.

There is a potential for survivors to decline consent, be lost to follow-up, or fulfil the exclusion criteria into the NEUROPACK study, and therefore, there is a risk that the survival subgroup may be biased. We plan to undertake sensitivity analyses by (1) imputing missing VABS II score for survivors using their known PICANet and NETPACK 3 data, (2) assume all survivors without a neurodevelopmental score had a VABS II score ≥70 and (3) assume all survivors without a neurodevelopmental score had a VABS II score <70, to ascertain impact of this group on the final prognostic model.

In addition, due to the limitations of not having a baseline VABS II score, we will also perform a secondary analysis using VABS II score ≥70 as the good neurodevelopmental outcome for a subgroup of patients with a known baseline PCPC score 1–3. This will allow comparison of the final prognostic model for all patients and the subgroup with known good neurodevelopment outcome at baseline.

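### Every death up to PICU discharge enters the primary model but only about 80% of survivors do, so inclusion depends on the outcome and the predicted probability of good outcome is calibrated to a selected sample

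*Protocol article*

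**What the plan says.** **Who enters.** The Sample size section states for deaths: "One hundred per cent of non-survivors will be included". It expects 80% of the survivors. The Exclusion section sets survivor-only conditions: "For children who survive to PICU discharge we will exclude patients where the local clinical team at participating sites feel inclusion is inappropriate", and the same sentence removes survivors whose family cannot follow the telephone interview in English. The recruitment section limits the consent approach to families of children thought likely to be alive at 3 months. The Data collections section links neurodevelopmental outcome to registry data only where there is consent.

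**What counts as poor.** The Primary outcome assessment section combines VABS-II below 70 and death.

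**What is held for the others.** Pseudonymised registry data are to be used for children who die and also "for patients who survive and consent for follow-up assessment is not available". The registry section adds: "PICANet collects survival to PICU discharge outcome data for all admissions".

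**How missing outcomes are handled.** The section on developing the prognostic model plans multiple imputation for variables with missing data considered in the model and does not say whether the outcome is one of them. The Secondary analysis section names refusal, loss and the exclusion criteria, concedes that "there is a risk that the survival subgroup may be biased", and answers with three sensitivity analyses: impute VABS-II, set all missing scores to 70 or above, set all to below 70.

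**How the model is finished.** The Final prognostic model section adjusts the intercept so that "the average predicted probability, is the same as the average observed probability".

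**The concern.** The model is meant for use within an hour of PICU admission, when nobody knows whether the child will survive. Its target population is therefore all eligible admissions. The development sample differs from that population in a way tied to the outcome: a child whose family speaks no English is in the sample if the child dies in PICU and out of it if the child survives.

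The result is an absolute probability, intended for talking with families and for stratifying care. Setting the intercept to the sample average builds the selected sample's rate into every prediction. The apparent calibration plot and the bootstrap use the same selected children, so neither can show the problem. Models for good outcome by PCPC or POPC follow the same steps and inherit it. So does the 3-month survival model wherever 3-month status is unknown.

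**Working it through.** **Inputs (Sample size section).** "we calculate 250 CA patients per year are admitted to 27 UK and RoI PICUs, 125 (50%) will survive to PICU discharge". Accrual lasts 18 months, with 370 patients, 80% of survivors included, 150 followed up and 75 with a good outcome.

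**Reproducing the plan.**
- Admissions: 250 × 1.5 = 375 (stated 370).
- Survivors: 375 × 0.50 = 187.5. Deaths: 187.5.
- Survivors followed up: 187.5 × 0.80 = 150, as stated.
- Good outcomes among them: 150 × 0.50 = 75, as stated.

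The 150 is met only if the 80% absorbs every kind of survivor loss: exclusions, refusal and loss to follow-up.

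**Rate in the full cohort and in the analysed sample, loss unrelated to VABS-II.**
- Full cohort: (187.5 × 0.50)/375 = 93.75/375 = 25.0%.
- Analysed: 75/(187.5 + 150) = 75/337.5 = 22.2%.
- Difference −2.8 points. Log-odds shift: ln(0.222/0.778) − ln(0.25/0.75) = −0.154, an odds ratio of 0.857.
- Starting from 370 gives the same percentages: 74/333 against 92.5/370.

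**Other base rates in the plan.** The same section also says "70 (30%) per year will survive with good neuro-developmental outcome". The count gives 70/125 = 56% of survivors, hence 28.0% overall and an analysed rate of (187.5 × 0.56 × 0.8)/337.5 = 84/337.5 = 24.9%. Taking the printed 30% instead gives 90/337.5 = 26.7% against 30.0%. The gap is about 3 points each time.

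**Effect on individual predictions.** Let r be the inclusion rate of survivors and q the share of a child's poor-outcome risk that is survival with VABS-II below 70. With random loss, the log-odds shift is ln r − ln(1 − (1 − r)q).
- r = 0.8, q = 1/3 (the plan's average: 93.75 poor survivors among 281.25 poor outcomes): ln(0.8/0.933) = −0.154. A true 50% is fitted as 46%, and 75% as 72%.
- q = 0 (all poor risk is death): ln 0.8 = −0.22. q = 1: no shift.

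The shift is thus largest where death dominates the poor-outcome risk, and one common intercept correction would not remove it exactly.

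**Where the bias sits.** A simulated cohort with one predictor, 50.1% survival, 24.7% good outcome and 80% random inclusion of survivors gave intercept −1.59 against −1.44 and slope −1.29 against −1.26, so the bias is mainly in the intercept. Applied to the whole simulated cohort, the mean prediction was 22.9% against 24.7%, a 1.8-point gap. That is smaller than the gap in the analysed rate, 0.8 × 24.7/(100 − 0.2 × 50.1) = 21.9% against 24.7%.

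**Loss that differs by outcome (assumed rates, averaging 80%).** The plan's figures give 93.75 good and 93.75 poor survivors.

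| Follow-up, good / poor | Good outcomes analysed | Analysed rate | Full cohort |
|---|---|---|---|
| 70% / 90% | 65.6 | 19.4% | 25.0% |
| 80% / 80% | 75.0 | 22.2% | 25.0% |
| 90% / 70% | 84.4 | 25.0% | 25.0% |
| 95% / 65% | 89.1 | 26.4% | 25.0% |

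**Bounds from the plan's own extreme scenarios.** There are 187.5 − 150 = 37.5 survivors without a score. All poor: 75/375 = 20%. All good: 112.5/375 = 30%.

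**The case against.** The strongest reply is that the plan already sees the problem. It names the sources of loss, commits to imputing VABS-II from registry data and brackets the answer with two extreme assumptions. The remaining dispute is which analysis leads. On the plan's figures the average shift is under 3 points, and relative ranking of risk is little affected. All of this is true. But the published coefficients and intercept come from the primary model, and a sensitivity analysis does not change the probability read out at the bedside.

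A second reply is that no sentence says survivors without a score are dropped: the imputation statement in the model-development section could be read to cover the outcome. That is a fair point about wording. However, listing VABS-II imputation as a sensitivity analysis makes sense only if the main model does not already do it. At the least the two sections need reconciling.

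Some stronger readings are not supported:
- *The model is certainly too pessimistic.* This holds if loss is unrelated to VABS-II. Approaching only families of children thought likely to live, and letting clinicians exclude survivors, could remove mainly poor-outcome survivors and cancel or reverse the bias.
- *The bias is much larger.* Survivor inclusion of 70% or 60% would give 20.6% or 18.8%, but those rates are assumptions; the plan states 80%.
- *All deaths to 3 months are captured.* Full capture is certain only to PICU discharge.
- *The 3-month survival model has no source for its outcome.* The article does not say how 3-month survival is ascertained in unconsented survivors, and an article may leave that to the full protocol.

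**Conclusion.** The concern stands. Inclusion in the primary model depends on the outcome by design, and the plan's correction sits outside the primary analysis. With 50% survival, half of survivors doing well, 80% of survivors included and loss unrelated to VABS-II, the rate to which the model is calibrated is 22.2% instead of 25.0%: about −2.8 points, or −0.15 on the log-odds scale, mainly in the intercept. If loss is related to outcome, neither size nor direction is fixed by the documents, and the plan's own scenarios allow a true rate from 20% to 30%. The conclusion rests on reading the Secondary analysis section as confining outcome imputation to sensitivity analysis, which is the more natural reading but is not stated outright.

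**What to change.** - Define the primary analysis set as all eligible children with known PICU survival status. Treat the survivor-only language and clinician-judgement criteria as reasons for a missing 3-month outcome, not as ineligibility.
- Multiply impute the missing 3-month outcome among PICU survivors, from the candidate predictors and other registry data held for all survivors. The imputation must be made within survivors; drawing the composite outcome without regard to known survival would carry the bias over. Alternatively, weight followed-up survivors by the inverse probability of follow-up, with PICU deaths at weight 1.
- Calibrate the final intercept to the imputed or weighted rate.
- Move the complete-case model to sensitivity, beside the two extreme-case analyses, and state in the model-development section that the outcome is imputed.
- Apply the same rule to the PCPC and POPC models and, where 3-month status is unknown, to the 3-month survival model.
- Do not use reason for non-consent as an imputation variable. The article does not say it is collected, and it would exist only where the outcome is missing.

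The cost is small: predictors and PICU survival are already held for unconsented survivors, and the imputation is already planned. The price is reliance on outcomes being missing at random among survivors given registry data. Selection by clinicians' prognosis may breach that, so the two extreme-case analyses must stay.

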### Identification and screening

Patients for the NEUROlogical Prognosis After Cardiac Arrest in Kids (NEUROPACK) study will be identified via entry into the PICANet database and by local researchers at each site screening PICU admissions daily. ‘CA preceding ICU admission—out of hospital or in-hospital’ is a specific high risk category in the PIM-3 risk adjustment model and is recorded within 1 hour of PICU admission, or within 1 hour of the attendance at the patient’s bedside of a specialist paediatric critical care team.^15^

### Recruitment for neurodevelopmental outcome assessment

Parent/guardians of CA patients who are expected to survive to 3 months following CA will be approached by local research staff, trained in Good Clinical Practice, to consent for telephone questionnaire at 3 months post-CA.

This is a very sensitive and difficult time for parents and guardians. The approach to parents or guardians of critical ill children for recruitment to the NEUROPACK study will, therefore, be handled sensitively. Local researchers will be trained to identify the appropriate time to consent, use passive information giving to reduce burden of information (eg, Ethics committee-approved posters displayed in family rooms) and liaise with the medical team managing the patient to acknowledge ongoing clinical management issues. Local site investigator (or delegate) will recontact parents or guardians at 2 months following CA to ascertain continued involvement in the study and to confirm ongoing contact details.

